### Strengths and limitations

The main strengths of this study are the randomised controlled design and the large sample size. The study includes a sample from a large heterogeneous population which should further a generalisation of our results to individuals on sickness absence in Denmark. Based on registers on sickness benefits, information on all individuals on sickness absence benefits in the source population were retrieved and thus, the study is not affected by incomplete coverage. The risk of bias related to group allocation is low since randomisation was performed by a computerised random number generator. To measure RTW, register data will be used, which is preferable compared to self-report in regard to receive more accurate information on the sick leave period [53]. To our knowledge, this is the first study to include measures of locus of control in this population. First of all, this assessment enables us to describe the external and internal locus of control of the individuals and then to assess whether it changes after PE. This particular questionnaire has not been validated in a Danish context; however, it has been translated, back-translated and pilot-tested in a group of individuals on sickness absence benefits.

The main weakness of this study is that the social workers were not effectively blinded. In collaboration with the individuals on sickness absence benefit, they assess whether the individuals are ready to RTW. About three months after the randomisation, we asked the social workers to guess what group they think the participant belongs to. Their guesses will show whether they have been aware of the group allocation. When examining the effect of an RTW intervention, such as PE, it is not possible to blind the participants or the staff, which may induce bias.

The results will contribute to the continuing research on sickness absence and mental health problems. It will primarily show whether PE can lead to faster and sustainable RTW and enable politicians and leaders of the job centres to decide whether the intervention should be implemented. Results will be available at the end of 2015.

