### Blinding

The social workers at the job centres were in contact with all study participants to provide the usual social services at the job centre, but they were not informed about their allocation in the study. Due to the nature of the intervention, neither participants nor staff could be blinded to the allocation.

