### Primary outcome

#### Sickness absence duration

Time to full RTW was the primary outcome of the study and was measured by register data from the job centres. It was defined as the period (in days) between randomisation and to *full-time* RTW for at least 4 weeks without (partial or full sickness absence) recurrence. Full return to work was operationalised as not receiving sickness benefits.

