#### Psychoeducation intervention

The PE used in this study was group-based, and the course consisted of 2 hour sessions once a week for 6 weeks. The course was in line with a slow-open group, meaning that new participants could be included shortly after they had accepted to participate. Receiving the intervention as fast as possible had a high priority. All courses were held at two different job centers; two locations were chosen to reduce transportation. Mileage allowance (0.27 euro/km) was offered to the participants.

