### Statistical analysis

It will be studied whether the participants differ from the eligible individuals who declined participation, and if the participants at follow-ups are different from the baseline population in relation to socio demographic and health characteristics. Adherence to the intervention will be described.

The rates of sustainable RTW will be compared between the intervention group and the control group during the first 3 and 6 months after randomisation by means of the pseudo value method [49, 50]. Any effects on psychological symptoms, mental health-related quality of life, and locus of control will be measured in secondary analyses. In those analyses symptoms of depression and anxiety will be the main outcome.

The analyses will be performed using STATA 11 IC (Stata Corp, College Station, TX).

All analyses will primarily be performed on an intention-to-treat basis; however, per-protocol analyses will also be performed [51].

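### The social workers' allocation guess at about three months cannot by itself show awareness of allocation, because by then they have seen, and helped decide, much of the return-to-work outcome

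*Protocol article*

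**What the plan says.** The Blinding section says the social workers saw all participants for the usual job-centre services but that "they were not informed about their allocation in the study". Under Strengths and limitations the article is more guarded: "The main weakness of this study is that the social workers were not effectively blinded". It explains that, together with the participant, "they assess whether the individuals are ready to RTW".

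The check on blinding is in the same paragraph: "About three months after the randomisation, we asked the social workers to guess what group they think the participant belongs to". The article then states what the answers mean: "Their guesses will show whether they have been aware of the group allocation".

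Three other statements fix where the guess falls in the trial:

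- Course length (Psychoeducation intervention): "the course consisted of 2 hour sessions once a week for 6 weeks".
- Main endpoint (section on sickness absence duration, under the primary outcome): "Time to full RTW was the primary outcome of the study and was measured by register data from the job centres".
- Analysis windows (Statistical analysis): RTW is compared "during the first 3 and 6 months after randomisation by means of the pseudo value method".

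The article describes no earlier guess, no certainty rating, no recorded reason for the guess and no breakdown by RTW status.

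**The concern.** A guess made at three months has at least two possible sources. The worker may have learned the allocation, or may have inferred it from how the participant has fared. The guess is taken after a six-week course would normally have ended, at a time that is itself one of the two windows for the RTW comparison, by people who take part in the decision to return. A worker who knows nothing can guess psychoeducation for those who are back at work and control for those who are not. If the course shortens absence, that habit yields more than half correct.

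The agreement between guess and allocation therefore cannot separate awareness from inference based on outcome, and the two are most easily confused when the course works. What is at stake is how a reader weighs the weakness that the article itself ranks first. An accuracy above one half could be taken as proof of awareness when it partly reflects a treatment effect.

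**Working it through.** **Inputs from the article.** Sample size calculation: 70% RTW within six months, hazard ratio 1.4, two-sided 5%, 80% power, minimum 397 participants. Randomisation: 1:1. Participants: 430 accepted (about 215 per arm) and 30 withdrew after randomisation.

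**The plan's own figure.** Schoenfeld events = 4 × (1.960 + 0.842)² / (ln 1.4)² = 277.3. Dividing by 0.70 gives 396.2, so 397. The stated minimum reproduces, so the 70% and the 1.4 are used as the protocol meant them.

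**Assumptions added here.** Constant hazards; 70% read as the control-arm figure (the article does not say which arm); 430 independent guesses; workers with no knowledge of allocation; a two-sided 5% test of guess against arm.

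**Step 1: RTW at three months.**

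- Control: 1 − 0.3^0.5 = 0.452
- Intervention: 1 − 0.3^(0.5 × 1.4) = 1 − 0.3^0.7 = 0.569

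**Step 2: accuracy of uninformed guesses.** Let a worker guess intervention with probability q if the participant has returned and 1 − q if not. Then accuracy = 0.5 + (2q − 1) × (0.569 − 0.452)/2. At q = 1 this is 0.5 + 0.117/2 = 0.559 to three decimals, against 0.5 by chance.

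**Step 3: chance that the assumed test is significant.** At q = 1 and 215 per arm, the difference in the proportion guessed intervention is 0.117. Its standard error is 0.0482 pooled and 0.0479 unpooled. Power = Φ[(0.1172 − 1.96 × 0.0482)/0.0479] = Φ(0.47) = 0.68. A simulation of 10,000 trials gave 0.67. With 200 per arm the figure is 0.65.

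| Reliance on RTW status (q) | Share correct | Significant at 5% |
|---|---|---|
| 1.0 | 55.9% | 68% |
| 0.9 | 54.7% | 49% |
| 0.8 | 53.5% | 31% |
| 0.7 | 52.3% | 16% |

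**Step 4: sensitivity at q = 1, 215 per arm.** Weibull shapes from 0.7 to 1.5, with the 70% read as control-arm or as overall, give 53% to 73%. A true hazard ratio of 1.2 gives about 25%. A hazard ratio of 1.0 gives about 4% to 5%, so the excess arises only when there is an effect.

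**Step 5: what stratifying does in this model.** Among those who have returned, the probability of guessing intervention is q in both arms; among those who have not, it is 1 − q in both arms. The association between guess and allocation disappears within each stratum. The strata would hold about 215 × (0.452 + 0.569) ≈ 220 and 215 × (0.548 + 0.431) ≈ 210 participants.

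**The case against.** A reader might infer that the article lays down a decision rule, that blinded workers would be declared unblinded, and that the trial would then discount its own positive result as assessor bias. The documents do not support this. The statement is one interpretive sentence in the discussion of limitations, with no test, threshold or null value. The Statistical analysis section does not mention the guess, and the RTW comparison is a pseudo-value analysis by intention to treat that does not depend on it. The article has already conceded that the workers were not effectively blinded, so a false signal would largely repeat the concession.

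The model is also stylised:

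- Some real awareness is plausible: participants knew their group and met these workers, the courses were held at two job centres, and a social worker co-taught one session.
- The 68% requires every guess to follow RTW status exactly and a true hazard ratio of 1.4.
- The number of guesses obtained is not reported.
- One worker may have guessed for many participants, so independence is doubtful.
- No document supports a particular guessing habit.

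All of this stands and limits the consequence. It does not rescue the inference. Conceding imperfect blinding does not make an ambiguous measure interpretable, and the ambiguity needs neither a formal test nor fully blinded workers. An article may leave the layout of a table to a fuller plan, but here it states what the guesses will establish, and that statement is too strong.

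**Conclusion.** The point holds as a limited one about interpretation. Guesses taken about three months after randomisation, by people who see and help decide RTW, cannot on their own show whether those people knew the allocation. In the base case uninformed guesses would be right about 56% of the time, and an assumed 5% test would be significant in about 68% of trials. Over the ranges tried the figure runs from 53% to 73% with full reliance on RTW status and from 16% to 49% in the base case with weaker reliance. It is about 5% with no effect. These are illustrations resting on assumed guessing behaviour, hazard shape, number and independence of guesses, and a test that the article does not specify.

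The ambiguity runs both ways: aware workers could themselves influence RTW, so an association between guess and allocation cannot be assigned to either cause. The primary estimate is untouched. This is a desirable improvement, not a threat to the trial's main conclusion.

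**What to change.** 1. Tabulate guess by allocation separately for participants who had and had not returned to work, by register status, on the date of the guess.
2. Replace *will show* with wording to the effect that the guesses may indicate awareness, and that overall accuracy alone cannot establish it because workers may infer the group from the participant's progress.
3. Read the within-status result cautiously. RTW status is itself post-randomisation, workers may respond to improvement short of RTW, and aware workers may influence RTW.

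The cost is one table and one sentence, using guesses and register dates already collected. The price is lower precision within strata (about 220 and 210 participants in the illustration instead of 430) and an ambiguity that is reduced but not removed.
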